Gladwish [29]	Phase I/II	Salv. (26)/Adj. (4)	51	3	65.57	66.3	102
Macchia [28]	Phase I/II	Salv. (18)/Adj. (106)	62.5	2.5	71.43	78.13	114.58
This study	Phase III	Salv. (288)	65	2.5	74.29	81.25	119.17

*EQD2* equivalent dose in 2-Gy fractions, *BED* biologically equivalent dose, *Salv.* salvage, *Adj.* adjuvant

^a^*α*/*β* ratio for prostate cancer is 1.5, 10 for early-responding normal tissue, and 3 for late-responding normal tissue

^b^Median

^c^Salvage

**Table 2 Tab2:** Literature review of hypofractionated radiotherapy outcomes for the treatment of prostate cancer in the postoperative setting

Study (ref.)	Median follow-up, months	bPFS, %	Toxicity scoring system	Acute toxicity, %		Late toxicity, %	
				GU	GI	GU	GI
Tandberg [30]	38.6	78.4^a^ (4 years)	CTCAE v4.0^b^/RTOG^c^	≥ G2: 22; G3: 1^d^	G2: 5; ≥ G3: 0	G2: 39; ≥ G3: 11	G2:10; G3: 1^d^
Kruser [33]	32.4	67 (4 years)	RTOG	G2: 6.4; G3: 1^d^	G2: 14; ≥ G3: 0	G2: 15; ≥ G3: 0	G2: 4; ≥ G3: 0
Lewis [31]	48	75 (4 years)	CTCAE v4.0^b^/RTOG^c^	G2: 4; ≥ G3: 0	G2: 4; ≥ G3: 0	G2: 39; G3: 28	≥ G3: 2^d^
Cuccia [32]	30	73 (3 years)	CTCAE v4.0	G2: 4; ≥ G3: 0	G2: 18; ≥ G3: 0	G2: 2.6; G3: 2.6	G2: 6.6; ≥ G3: 0
Barra [34]	15.5	Not reported	CTCAE v4.0^b^/RTOG^c^	≥ G2: 0	≥ G2: 0	G2: 3.3; G3: 3.3	≥ G2: 0
Alongi [35]	22.8	Not reported	RTOG	G2: 10; ≥ G3: 0	G2: 20; ≥ G3: 0	G2: 8; G3: 3	≥ G2: 0
Saldi [27]	27	Not reported	CTCAE v4.0	G2: 8.9; ≥ G3: 0	G2: 9.8; ≥ G3: 0	Not reported	Not reported
Katayama [26]	Not reported	Not reported	CTCAE v4.0	≥ G2: 0	G2: 17.9; ≥ G3: 0	Not reported	Not reported
Gladwish [29]	24	Not reported	CTCAE v3.0^b^/RTOG^c^	G2: 3; G3: 3	≥ G2: 0	≥ G2: 1^d^	≥ G2: 2^d^
Macchia [28]	30	86.5 (5 years)	RTOG	G2: 17.7; G4: 1^d^	G2: 24.2; ≥ G3: 0	≥ G2: 7.3	≥ G2: 1.1

*bPFS* biochemical progression-free survival, *GU* Genitourinary, *GI* gastrointestinal

^a^Patients with a 12-month minimum follow-up were analyzed for bPFS

^b^Acute

^c^Late

^d^Number of patients

The protocol of the Salvage hypofractionated accelerated versus standard radiotherapy for biochemical recurrence after radical prostatectomy (SHARE) study is outlined here. This prospective, randomized, multi-institutional trial is designed to assess whether HRT improves biochemical control versus CRT without increasing treatment toxicity in prostate cancer patients with biochemical recurrence after radical prostatectomy. This study uses two RT dose schemes, HRT (65 Gy in 2.5-Gy fractions) versus CRT (66 Gy in 2-Gy fractions).

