### Data collection and follow-up period

Patient data will be collected according to the schedule shown in Fig. 2, i.e., prior to initiating RT, weekly during RT, every 3 months for the first 2 years after RT, every 6 months for years 3–5, and then annually thereafter. The following patient data will be recorded in case report forms: urologic/gastrointestinal (GI) toxicities using the Common Toxicity Criteria for Adverse Events (CTCAE v5.0), patient-reported outcomes, QoL, and PSA levels. A pop-up sticker note will be generated automatically on the electronic medical record system to improve adherence to intervention protocols and follow-up laboratory tests. These outcome data will be aggregated as median and interquartile range. If tumor recurrence or metastases are suspected, pelvic magnetic resonance imaging, CT, and/or bone scans can be performed at the discretion of the investigator.

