### Assessment of primary and secondary endpoints

The primary endpoint is to investigate whether HRT improves 5-year bPFS versus CRT in patients with biochemical recurrence after radical prostatectomy. Biochemical progression-free survival is counted from the date of the salvage radiotherapy to biochemical progression, clinical progression, or death of any cause. Biochemical progression after RT is defined as detectable PSA after salvage RT. Secondary endpoints are to compare acute and late toxicities based on CTCAE v5.0 and QoL and to determine 5-year distant metastasis-free survival (DMFS) and cancer-specific survival (CSS).

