### Sample size considerations and statistical analysis

The trial is powered to assess the superiority of HRT when compared with CRT. Power calculations are based on an absolute increase in bPFS of 15% (from 50 to 65%) at 5 years following HRT compared with CRT according to the dose-response relationship described by King [9]. By postulating a minimum 5-year follow-up period and allowing 5% for loss, at least 144 patients per treatment arm (288 patients in total) are required, which achieves 80% power, with a two-sided *α* of 0.05. Subgroup analyses will be performed based on the risk group (intermediate vs. high-risk group), RT field size (prostate bed only vs. elective pelvic nodal irradiation), and use of ADT.

Statistical analysis will be conducted according to the intention-to-treat approach. Survival data, PSA value, toxicity, and QoL information will be collected even though participants discontinue the planned treatment. Multiple imputation method will be used for handling missing data. The chi-square test and Student’s *t* test will be used for categorical and continuous variables of patient characteristics, respectively. Time to biochemical progression will be calculated from the end of RT. The Kaplan–Meier method will be applied to estimate bPFS curves, and the log-rank test will be used to compare the curves between the two study arms. The Kaplan-Meier method and log-rank test will be used to investigate DMFS and CSS. Acute toxicity outcomes and QoL will be estimated using the chi-square test, and late toxicity outcomes will be determined using the Kaplan-Meier method.

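### QoL, a score measured before RT and repeatedly afterwards, is assigned a chi-square test; acute toxicity may keep that test but needs a risk difference with a confidence interval

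*Protocol article*

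**What the plan says.** The statistical section of the protocol article names the test: "Acute toxicity outcomes and QoL will be estimated using the chi-square test". Late toxicity is assigned to the Kaplan-Meier method. For patient characteristics, the same section uses chi-square for categorical variables and Student's t test for continuous ones.

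Under Data collection and follow-up period, toxicity, patient-reported outcomes, QoL and PSA are recorded "prior to initiating RT, weekly during RT, every 3 months for the first 2 years after RT, every 6 months for years 3–5", then annually. On summarising them: "These outcome data will be aggregated as median and interquartile range".

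The article describes the toxicity question in two ways. The Background gives the aim as "whether HRT improves biochemical control versus CRT without increasing treatment toxicity in prostate cancer patients". The endpoint section is more modest: "Secondary endpoints are to compare acute and late toxicities based on CTCAE v5.0 and QoL". The sample size is set for bPFS only: "The trial is powered to assess the superiority of HRT when compared with CRT". No power, margin or precision is stated for toxicity or QoL.

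**The concern.** A chi-square test compares category counts between independent groups. A median and interquartile range describe a quantitative score. To apply the test to QoL, the score must first be cut into categories, either at one visit or visit by visit. The article gives no cut-point, responder definition or key visit. As written, the pre-treatment value and the series of later values have no stated role. The likely costs are lost power and, if the test is repeated over visits, extra chance findings.

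For acute toxicity the problem is narrower. The Background promises to find out whether control improves with no increase in toxicity, while the named test only looks for a difference. If p > 0.05 were taken as the answer, a moderate real increase could be reported as no increase. The article's Discussion treats genitourinary and gastrointestinal toxicity as key obstacles to hypofractionation in this setting, so the wording of that conclusion matters.

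**Working it through.** **Sample size carried forward.** The plan's only figure is 288 in total (144 per arm), for bPFS. It reproduces closely:
- HR = ln 0.65 / ln 0.50 = 0.621.
- Schoenfeld events = 4 × (1.960 + 0.842)² / (ln 0.621)² ≈ 139.
- Assuming exponential survival, uniform accrual over about 2.6 years (August 2019 to March 2022) and 5 years' minimum follow-up, the event probability is 0.499. So N = 139 / 0.499 ≈ 279, and 279 / 0.95 ≈ 294, against 288 stated (about 2% apart).

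This figure does not depend on the present point. What carries over is 144 × 0.95 = 136.8, or 137 evaluable per arm.

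**QoL.** Assumptions not in the documents: normally distributed score, true difference 0.3 SD, two-sided 0.05, and a median split wherever the score is dichotomised.

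*Chi-square on a median split.* The proportions above the cut are Φ(−0.15) = 0.440 and Φ(0.15) = 0.560. Power = Φ[(d − 1.96 × SE0) / SE1], with
- d = 0.119
- SE0 = √(2 × 0.5 × 0.5 / 137) = 0.0604
- SE1 = √(2 × 0.440 × 0.560 / 137) = 0.0600

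This gives Φ(0.014) = 51%.

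*Means.* Power = Φ[0.3 / (√(1 − ρ²) × √(2/137)) − 1.96], where √(2/137) = 0.1208 and ρ is the correlation of the later score with baseline.

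| Analysis | Standard error (SD units) | Power at 0.3 SD |
|---|---|---|
| Chi-square, median split | – | 51% |
| Means, unadjusted | 0.121 | 70% |
| Means, adjusted, ρ = 0.3 | 0.115 | 74% |
| Means, adjusted, ρ = 0.5 | 0.105 | 82% |
| Means, adjusted, ρ = 0.7 | 0.086 | 94% |

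At 0.4 SD the median-split chi-square has 75% power and unadjusted means 91%.

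**Acute toxicity.** The same two-proportion formula with 137 per arm is used. The 8% and 22% are the conventional and hypofractionated rates of acute grade ≥ 2 GU toxicity in the retrospective comparison cited in the Discussion. The intermediate rates are assumed.

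| True rates | Power | Chance of p > 0.05 |
|---|---|---|
| 8% vs 22% | 90% | 10% |
| 8% vs 16% | 53% | 47% |
| 8% vs 15% | 44% | 56% |
| 8% vs 13% | 27% | 73% |

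Worked row, 8% vs 16%: mean rate 0.12; SE0 = √(2 × 0.12 × 0.88 / 137) = 0.0393; SE1 = √((0.08 × 0.92 + 0.16 × 0.84) / 137) = 0.0390; Φ[(0.08 − 1.96 × 0.0393) / 0.0390] = Φ(0.08) = 53%.

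Precision: with equal rates, the 95% CI half-width for the risk difference is 1.96 × √(2p(1 − p)/137), which is 6.4 points at p = 8% and 9.8 points at p = 22%.

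**The case against.** For acute toxicity, much of the opposing case stands. Chi-square is a standard comparison of the proportions reaching a given CTCAE grade, and it has about 90% power for the one between-arm contrast that the article cites. Nothing in the article says that p > 0.05 will be read as proof of no increase or that confidence intervals will be withheld. The endpoint section promises only a comparison. A margin for a secondary endpoint may sit in the full protocol or the analysis plan, so its absence is not held against the article. The test sentence also covers acute toxicity only, whereas the Background aim extends to late toxicity.

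A reader might infer that a non-significant result is to be expected even if toxicity doubled. The figures do not support that. A doubling from 5% to 10% has 35% power, from 8% to 16% 53%, and from 10% to 20% 64%. Such a result could easily occur at low rates, but it is not the rule.

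For QoL, a chi-square on a categorised change from baseline is a recognised responder analysis and would use the baseline in part. The article neither states nor excludes this, so a flat claim that baseline is discarded goes too far. A reader might also multiply the efficiency of a median split (2/π = 0.64) by the gain from baseline adjustment (1 − ρ² = 0.75 to 0.51 for ρ = 0.5 to 0.7) and conclude that only a third to a half of the information is used. That depends on a cut-point, a distribution and correlations that the documents do not give, and part of the loss would also affect an unadjusted t test.

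These objections do not remove the QoL point. The article itself chooses the categorical test for data that it summarises as a quantitative score, so this is a stated choice rather than a detail left to the analysis plan.

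**Conclusion.** The QoL point holds. The named test does not suit a score with a baseline and repeated follow-up, and it sits badly with the article's own median and interquartile range summary. The power figures of about 51%, 70% and 82% show the possible cost. They assume 137 per arm, a 0.3 SD difference, a median split and a baseline correlation of 0.5, and they are not an estimate of what this trial will lose.

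The toxicity point holds only in a narrow form. Chi-square is not the error. The Background aim and the endpoint section promise different things, and a difference test alone can answer only the second. With 137 per arm the test would probably detect an increase as large as 8% to 22%, but would miss 8% to 16% in about 47% of trials.

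The primary analysis and its sample size are unaffected. The change is worth making before analysis.

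**What to change.** 1. **QoL and patient-reported scores.** Replace chi-square as the main analysis with a mixed model for repeated measures containing arm, visit, arm-by-visit interaction, baseline score and NCCN risk stratum, and name one key time point. A chi-square on a prespecified responder definition may stay as a supportive analysis.
2. **Toxicity.** Keep chi-square for acute toxicity, but add the between-arm risk difference with a 95% CI. For late toxicity, add the between-arm difference in cumulative incidence with a 95% CI.
3. **Wording.** Base any statement of no increase on the upper confidence limit, never on p > 0.05. Otherwise, align the Background aim with the endpoint section, which only compares toxicity.

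Cost: a change of wording in the protocol or analysis plan and modest analysis work, with no new data, visits or patients. The visit structure and the key time point must be specified in advance, and the toxicity conclusion may become more cautious.

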## Discussion

By increasing the radiobiological dose delivered to the prostate, HRT has the potential to shorten the duration of treatment, thereby improving patient convenience and reducing healthcare costs. In the past two decades, HRT in the intact prostate cancer setting has been evaluated in randomized controlled trials, demonstrating this approach as a safe and effective alternative to CRT. However, the efficacy and toxicity of HRT in the postoperative treatment setting remain to be validated. Several retrospective or phase I/II studies of HRT in the postoperative setting have used heterogeneous dose schemes and toxicity scoring systems, making it difficult to interpret the results. No data from randomized studies of HRT in the management of patients with biochemical recurrence after radical prostatectomy are currently available.

Biochemical control after HRT using modern RT techniques in the postoperative setting has been seen to be favorable in several studies. The studies by Tandberg et al., Kruser et al., and Lewis et al. used a HRT scheme of 65 Gy in 2.5-Gy fractions (EQD2 = 74.29 Gy; *α*/*β* ratio = 1.5 Gy), demonstrating a 4-year bPFS of 78.4, 67, and 75%, respectively [30, 31, 33]. In particular, Tandberg et al. retrospectively compared oncologic outcomes between HRT (*n* = 167) and CRT (*n* = 294) [30]. With a median follow-up of 52 months, 4-year bPFS was 78.4% after HRT and 64.8% after CRT (*P* = 0.0038). On multivariate analysis, there was a trend for decreased risk of biochemical progression in the HRT group compared with the CRT group (*P* = 0.059). Cuccia et al. reported a 3-year bPFS of 73% in 75 patients treated with salvage or adjuvant aims, but the prescribed dose (63.8 Gy in 2.2-Gy fractions; EQD2, 67.45 Gy) was relatively low compared with those used in other HRT studies [32]. The phase I/II study by Macchia et al. used RT with the 62.5 Gy in 2.5-Gy fractions scheme (EQD2 = 71.43 Gy) and reported a 5-year bPFS of 86.5% [28]. However, the study included a relatively small number of patients receiving RT with a salvage aim (18 of 124 patients). Therefore, to date, significant heterogeneity in the dose scheme and treatment aims (both salvage and adjuvant) means that it is difficult to draw conclusions regarding the oncologic treatment outcomes of salvage HRT.

Genitourinary (GU) and GI toxicities are considered to be key obstacles to the administration of HRT for prostate cancer in the postoperative setting. Although different toxicity scoring systems used in previous studies have made it difficult to assess the safety of HRT in the postoperative setting, most have demonstrated a tolerable toxicity profile [26–28, 30, 31, 33–36]. Kruser et al. (65 Gy in 2.5-Gy fractions) reported low rates of toxicity (one acute grade 3 GU toxicity, no acute grade 3 GI toxicities, and no late grade 3 toxicities) in 108 salvage RT patients [33]. Tandberg et al. evaluated HRT (65 Gy in 2.5-Gy fractions) in 167 patients and CRT (66 Gy in 1.8–2.0-Gy fractions) in 294 patients to determine any differences in toxicity between the two treatment groups [30]. The results showed that acute grade ≥ 2 GU toxicity was more common after HRT (22 vs. 8% in the CRT group, *P* = 0.0001), but HRT was not associated with late grade ≥ 2 GU toxicity on multivariate analysis. In the study by Barra et al., late grade 3 GU toxicity was recorded in 3.3% of 64 patients who received RT with a dose scheme of 62.5 Gy in 2.5-Gy fractions [34]. Alongi et al. reported no toxicities ≥ grade 3 in 39 patients who received RT with a median dose of 70 Gy in 2.5-Gy fractions [35]. A single acute grade 4 GU toxicity event was reported by Macchia et al. (62.5 Gy in 2.5-Gy fractions) [28]. In the Lewis et al. study, toxicity events > grade 3 were unusual in patients with a median dose of 65 Gy in 2.5-Gy fractions, although a relatively high rate of late GU toxicity was seen, noting a 4-year actuarial rate of late grade 3 GU toxicity of 28%, which was exclusively gross hematuria [31]. With a median follow-up of 48 months, most cases of grade 3 GU toxicity resolved, with only 7% persisting at the last follow-up visit. Analyses of bladder dose volume and PTV volume revealed no significant differences between patients with and without grade 3 GU toxicity. The authors suggested that potential explanations for the high rate of late GU toxicity could include the longer follow-up times and differences in treatment imaging and radiation delivery versus other studies, although the precise reason was not clear. Acute and late toxicities associated with HRT in the postoperative setting were relatively acceptable in most studies.

As phase III trials have demonstrated the benefits of ADT in the definitive RT setting, the addition of ADT to salvage RT may be beneficial in some patients. However, the optimal timing, duration, and type of hormone treatment remain to be determined. Two phase III trials advocated the use of ADT for patients who received salvage RT. The RTOG-9601 trial, a placebo-controlled phase III study, demonstrated that the addition of 24 months’ ADT with daily bicalutamide to salvage RT resulted in significantly higher rates of overall survival (76.3 vs. 71.3% in patients receiving placebo; *P* = 0.04), and a lower incidence of metastatic prostate cancer (14.5 vs. 23%, respectively; *P* = 0.005), and death from prostate cancer (5.8 vs. 13.4%, respectively; *P* < 0.001) at 12 years [40]. Another randomized trial, GETUG-AFU 16, has also shown the superiority of adding 6 months of goserelin to salvage RT [41, 42]. After a median follow-up of 112 months, the 10-year progression-free survival was significantly better in the ADT arm versus RT alone (64 vs. 49%, respectively; *P* < 0.0001). The RADICALS trial randomly assigned patients to adjuvant RT or salvage RT, with or without ADT, and the NRG Oncology/RTOG 0534 SPPORT trial randomly assigned patients to salvage RT to the prostate bed, salvage RT to the prostate bed with ADT, or salvage RT to the prostate bed and the pelvic lymph nodes with ADT. The results of these trials could provide further evidences concerning the administration of postoperative ADT. To date, it is uncertain whether ADT in combination with salvage HRT improves biochemical control. In the trial outlined here, the authors will conduct subgroup analyses according to the use of ADT and examine the benefit derived from combined therapy. We anticipate that HRT will demonstrate favorable biochemical control and acceptable toxicity in prostate cancer patients with biochemical recurrence after radical prostatectomy. If HRT is seen to be superior to CRT, it will indicate the benefit of escalating dose delivery to the prostate bed, which will also improve patients’ convenience and reduce healthcare costs.

## Trial status

The current protocol is version 1.6 as of 4 February 2021. Patient recruitment began in August 2019 and is expected to be completed by March 2022.

## Data Availability

The datasets used during the current study are available from the corresponding author on reasonable request.

## Abbreviations

PSA: Prostate-specific antigen
RT: Radiotherapy
bPFS: Biochemical progression-free survival
SAKK: Swiss Group for Clinical Cancer Research
IMRT: Intensity-modulated radiotherapy
HRT: Hypofractionated radiotherapy
CRT: Conventionally fractionated radiotherapy
QoL: Quality of life
NCCN: National Comprehensive Cancer Network
EQ D2: Equivalent dose in 2-Gy fractions
BED: Biologically effective dose
ADT: Androgen deprivation therapy
CT: Computed tomography
CTV: Clinical target volume
PTV: Planning target volume
GI: Gastrointestinal
CTCAE: Common Toxicity Criteria for Adverse Events
DMFS: Distant metastasis-free survival
CSS: Cancer-specific survival
GU: Genitourinary
